### Aims of the study

The primary aim of the CONECSI (COping with NEuropathiC Spinal cord Injury pain) trial is to evaluate the effectiveness of a multidisciplinary cognitive behavioural programme for coping with CNSCIP. The intervention is expected to result in decreased pain intensity and pain-related disability, and in higher levels of mood, participation in activities, and life satisfaction. The secondary aim is to examine post-hoc (explorative) the influence of demographic and lesion characteristics, pain coping and pain cognitions on the effect of the intervention and the relation between the change of coping and cognitions and the effectiveness of the intervention. It is expected that the intervention will be most effective in persons who show dysfunctional pain cognitions and pain coping strategies before the intervention and in persons who show a change in pain coping and pain cognitions in a positive direction. The third aim is to examine the satisfaction of the participants and trainers about the intervention and to explore which parts will be regarded as effective. This paper describes the design of the CONECSI trial and the content of the programme.

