### Participants and procedure

Physiatrists from the four rehabilitation centres select former patients from their centre meeting inclusion criteria 1, 2, and 3 (Table 1). The selected persons will be sent a questionnaire to determine if they meet the inclusion (4, 5, and 6) and exclusion (1) criteria. In an interview with the psychologist, who will conduct the programme, will be checked for the other exclusion criteria and will be asked for written consent before final inclusion in the CONECSI trial. Included participants will be randomised (stratified by rehabilitation centre) to the intervention group or the waiting list control group (Figure 1). Measurements will be performed in both groups before starting the programme or entering the control group (t1), at 3 (t2), 6 (t3), 9 (t4), and 12 months (t5) follow-up. The control group will be invited for the programme after the follow-up measurement at 6 months.

**Table 1 T1:** In-and exclusion criteria

Inclusion criteria
(1) SCI

(2) at least 18 years old

(3) at least one year after discharge from first inpatient SCI rehabilitation

(4) main pain type is neuropathic pain

(5) duration of neuropathic pain of at least six months

(6) pain intensity score in the previous week of at least 40 on the 0-100 numerical rating scale of the Chronic Pain Grade

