### Data analysis

This trial with repeated measurements nested in each patient will be used to evaluate differences in effect between the intervention group and the waiting list control group. Differences between groups, with 95% confidence intervals, will be calculated for the outcome measures: CPG, HADS, UAL, and LiSat-9, by random coefficient (multilevel) analyses. The effectiveness of the intervention will be tested by analysing differences between the intervention group and the waiting list control group in the course of outcomes over time (0, 3, and 6 months, respectively t1, t2, and t3). Further, the long-term (6, 9, and 12 months, respectively t3, t4, and t5) impact of the intervention will be analysed in participants randomised to the intervention group. The impact of demographic and lesion characteristics, pain cognitions and pain coping on the effectiveness of the intervention will be studied explorative by merging data from the intervention group (t1, t2, t3) and the waiting list group (t3, t4, t5). Both the impact of differences at baseline, and changes in pain cognitions and pain coping during and after the intervention will be post-hoc analysed. Factor rehabilitation centre will be controlled for in the effectiveness analyses, but post-hoc analyses of differences between rehabilitation centres will be analysed and combined with information on compliance and patient satisfaction to identify determinants of a successful intervention. Data will be analysed according to the intention-to-treat principle. SPSS statistical program for Windows (version 16.0) and the MLwiN program of the Centre for Multilevel Modelling, Institute of Education, University of London (version 2.02) will be used for the analyses. Significance level will be set at a p-value less than .05.

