## Discussion

This multidisciplinary cognitive behavioural programme for coping with CNSCIP will be evaluated in a multicentre trial, in which 60 persons will be randomised to an intervention group or a waiting list control group in four participating rehabilitation centres. The CONECSI trial meets the need for an RCT for the evaluation of CBT for people with CNSCIP, focusing on reduction of negative pain cognitions and promoting adaptive coping. This intervention is expected to contribute to the treatment options for people with CNSCIP, a severe problem for which existing treatments are insufficiently effective.

This study will have the advantage of a randomised control group over other studies like Norrbrink Budh and colleagues [8]. Our use of a waiting list control group that will be invited for the intervention six months after the intervention group has potential advantages. First of all, the people who will be randomised in the waiting list group will also be given the opportunity to participate in the intervention. This prospective might minimize demoralization and enhance participation of people in the waiting list group. Second, the possible impact of pain coping and pain cognitions on the effectiveness of the intervention can be examined in twice as many people.

The intervention consists of an eclectic and multidisciplinary treatment programme: a combination of education, relaxation and activation, and using different theoretical models that are complimentary to each other. If the intervention as a whole is effective, this will make it more difficult to point out the effective elements of the intervention. But we expect to include participants with a variety of pain cognition and pain coping behaviours (for example, an active coping over-user and a passive coping, high catastrophizing under-user) and therefore we choose to present information on different topics and in different ways. The expected advantage is that, this way, each participant will find something useful in the programme.

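### The analysis of who benefits uses merged data in which everyone is treated, so it can show predictors of change but not moderators of effect

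*Protocol article*

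**What the plan says.** Under Aims of the study: "The secondary aim is to examine post-hoc (explorative) the influence of demographic and lesion characteristics, pain coping and pain cognitions on the effect". A direction is given: "It is expected that the intervention will be most effective in persons who show dysfunctional pain cognitions and pain coping strategies before the intervention", and likewise in those whose coping and cognitions change favourably.

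Under Data analysis, the main effect is tested between the randomised groups "in the course of outcomes over time (0, 3, and 6 months, respectively t1, t2, and t3"). The influences on effectiveness are handled differently: the impact of these factors "on the effectiveness of the intervention will be studied explorative by merging data from the intervention group" at t1, t2 and t3 with data from the waiting list group at t3, t4 and t5. Baseline differences and changes in cognitions and coping are both to be analysed this way.

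Under Participants and procedure: "The control group will be invited for the programme after the follow-up measurement at 6 months". Table 1 requires a "pain intensity score in the previous week of at least 40" for entry.

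The Discussion counts the merge as an advantage of the waiting-list design, because the impact of coping and cognitions "can be examined in twice as many people".

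**The concern.** A moderator is a variable on which the difference between treated and untreated people depends. The merged data set contains no untreated people. A baseline variable that predicts change there may be a modifier of the effect, a prognostic factor for the natural course, or a marker of regression to the mean, and the analysis cannot tell these apart. That holds for every candidate, including demographic and lesion characteristics, whatever correlations are assumed.

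For cognitions and coping there is a further risk. If someone reports worse cognitions on a day when pain is also unusually bad, both will tend to ease later. Worse baseline cognition then goes with larger improvement even if the programme helps everyone equally, which is the direction the protocol expects.

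At stake is the secondary aim. An association could be reported as showing whom the programme suits and be used to select patients.

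**Working it through.** **1. Who is treated in each period**

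| Group | t1–t3 | t3–t5 |
|---|---|---|
| Intervention | programme and follow-up; in the merge | not in the merge |
| Waiting list | untreated; not in the merge | programme and follow-up; in the merge |

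Every record in the merge comes from a treated period.

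**2. Measurements available (Table 2 as extracted).** The three coping and cognition questionnaires are marked for both groups at T1 and T2, for the intervention group only at T3, for nobody at T4, and for the waiting list only at T5. Of the three waiting-list occasions to be merged, only t5 has these scores. Its pre-programme point (T3) and the next measurement (T4) are missing. The outcome measures are marked at all five occasions in both groups.

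**3. Sample size used.** The protocol gives no figure for the moderator analysis. The Power analysis section gives 24 per arm, 48 in all, and 60 with dropout. With a difference of 16 and SD 17, 2 × (1.960 + 1.282)² × (17/16)² = 23.7, so 24 per arm, and 48/0.8 = 60. This reproduces the figure with a two-sided 5% test and 90% power; the one-tailed test named there would give 19.3, so 20. Nothing below depends on that label.

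**4. When regression to the mean produces the pattern.** Let C be baseline cognition, X baseline pain and Y later pain, with X and Y of equal variance and correlation ρ. An effect identical in everyone shifts Y by a constant, so

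Corr(C, Y − X) = (r_CY − r_CX) / √(2(1 − ρ)).

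- If C relates to later pain only through baseline pain, r_CY = ρ·r_CX. With ρ = 0.6 and r_CX = 0.5: (0.3 − 0.5)/√0.8 = −0.224. In simulation at n = 48, a 5% test rejects in 41%, 34%, 28% and 18% of trials for ρ = 0.5, 0.6, 0.7 and 0.8.
- If C relates equally to pain at both times, the numerator is zero and rejection is 5–6%.
- Halfway between: 14%, 12%, 10% and 8%.

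**5. Simulation with entry at pain of at least 40.** There were 1,500 trials per cell, n = 48 or 60, and a 16-point effect in everyone, so true moderation is zero. Each segment was simplified to one before and one after measurement. From the documents: the entry threshold, and PCL-2003 stability of 0.51 and 0.73. Assumed: pain stability 0.5 and 0.7; correlation of 0.4 between the stable parts of pain and cognition; correlation of 0, 0.3 or 0.5 between their occasion-specific parts; and a pre-selection pain mean of 58 and SD of 21. After selection, baseline pain had mean about 65 and SD about 16, against 64.7 and 17.0 in the protocol.

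| Occasion-specific correlation | Merged slope (pain change per SD of worse cognition) | Merged test rejects | Change-on-change rejects | Randomised interaction rejects |
|---|---|---|---|---|
| 0 | +0.2 to +0.6 | 4–6% | 4–6% | 5–6% |
| 0.3 | −1.3 to −2.5 | 8–14% | 53–65% | 4–6% |
| 0.5 | −2.6 to −4.6 | 16–41% | 94–98% | 5–6% |

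Hand check, ignoring selection: the slope is −21 × √((1 − 0.5)(1 − 0.51)) × 0.5 = −5.2, against −4.6 simulated in that cell; selection on pain attenuates it.

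Adjusting the merged analysis for baseline pain did not reliably help (slopes −1.5 to +2.6, rejection 4–17%). The interaction estimate averaged −0.2 to +0.3 points per SD, with a standard error about 2.0 times that of the merged slope.

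**6. Effect of the missing T3 score.** Step 5 gave the waiting list a cognition score on the day of its starting pain, which Table 2 does not provide. If that half uses an earlier score, equally correlated with t3 and later pain (assumption), the step 4 rates at r_CX = 0.5 fall from 18–41% to 13%, 12%, 10% and 9%.

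**The case against.** The strongest defence is that the analysis is openly exploratory and post hoc, that no confirmatory claim rests on it, and that its exact model may be in an analysis plan not shown. This limits the weight of the point but does not answer it. The label speaks to multiplicity and strength of evidence; it does not turn change in treated people into a treatment effect. The choice of data set is stated in the protocol itself.

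A second defence concerns size, and much of it stands. The upper false-positive rates need baseline cognition and pain to share occasion-specific variation, or cognition to predict later pain only through baseline pain. Some sharing is plausible for self-report at one sitting, but the documents give no figure. For half the merged sample the scores are not even taken on the same occasion (step 6).

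Stronger readings are tempting. A reader might infer that the analysis is bound to confirm the expected pattern; step 4 shows that it need not. A reader might infer that the two halves regress unequally because the intervention group's t1 comes soon after selection. The simulation gave a drop of 2.0 to 3.8 points from t1 in that group and about 0 from t3 in the waiting list, but only because entry was modelled at t1; the protocol gives no interval between screening and t1. Nor is regression to the mean the whole explanation. For demographic and lesion characteristics the problem is mainly prognosis versus modification, and for change-on-change it is shared occasion variation without control for the natural course.

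Finally, interactions are imprecise in a trial sized for the main effect. That is true, and it is the price of a controlled comparison.

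**Conclusion.** The point holds as a flaw in the secondary aim and should be corrected. The merged analysis cannot identify moderators of effect, and that conclusion needs no numerical assumption. The possible inflation in favour of the expected pattern does: the false-positive rate of a 5% change-score test on baseline cognition runs from about 5% with no shared occasion variation to about 40% under strong assumptions, and is lower where the waiting list's score predates its t3 pain. The change-on-change analysis is more exposed if such variation is shared. The merge is also not feasible as described for coping and cognitions, if Table 2 is as extracted.

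A reader might conclude that the randomised controls are lost to the trial. They are not: the primary comparison stays between groups over t1–t3 and is unaffected. Only the waiting list's control period goes unused, and only in this analysis.

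**What to change.** - Test group × baseline (t1) moderator interactions on the outcomes in the randomised t1–t3 data of both groups. Start with catastrophizing and passive coping, the predictors singled out in the Background, and name the subscales, since the three questionnaires have 8 + 6 + 5 = 19. Keep this exploratory and report confidence intervals.
- Relabel the merged analysis, including change-on-change, as a description of predictors of course in treated participants.
- State which measurement serves as the waiting list's pre-programme coping and cognition score, and reconcile Table 2 with the Data analysis section.
- Report any model using t1–t2 coping change as associational, even with group in the model, because it conditions on a post-randomisation variable.

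The cost is wording and analysis time; the interaction test needs no new data. The downside is precision: with a standard error about twice that of the merged slope, about four times (2² = 4) as many people would be needed for equal precision, so wide intervals should be expected.

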**Pain coping and pain cognitions**						

Pain coping	Coping Strategy Questionnaire	X	X	X^I^		X^C^
	Pain Coping Inventory	X	X	X^I^		X^C^
Pain cognitions	Pain Cognition List	X	X	X^I^		X^C^

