**Other measures**						

Demographic variables (age, gender, marital status, and education)		X				

SCI and pain characteristics		X				

Neuropathic pain treatment		X	X	X	X	X

Functional independence	Barthel Index	X				

Satisfaction with intervention	Questionnaire on satisfaction		X^I^		X^C^	

X: intenvention group and waiting list control group

X^I^:only intervention group

X^C^: only waiting list control group

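### The pooled coping and cognition analysis needs waiting list scores at t3 and t4 that Table 2 does not collect

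*Protocol article*

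**What the plan says.** The Data analysis section of the protocol article describes an exploratory analysis of what influences the programme's effect: demographic and lesion characteristics, pain cognitions and pain coping. It is to be done "by merging data from the intervention group (t1, t2, t3) and the waiting list group (t3, t4, t5"). For the coping and cognition scores the section is specific about what is wanted: "Both the impact of differences at baseline, and changes in pain cognitions and pain coping during and after the intervention will be post-hoc analysed".

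The Discussion presents this pooling as the second potential advantage of the waiting list design, because "the possible impact of pain coping and pain cognitions on the effectiveness of the intervention can be examined in twice as many people".

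Table 2 has one row each for the "Coping Strategy Questionnaire" (CSQ), the "Pain Coping Inventory" (PCI) and the "Pain Cognition List" (PCL). All three rows read the same: both groups at T1 and T2, X^I at T3, nothing at T4, X^C at T5. The legend defines X^I as "only intervention group" and gives "X^C^: only waiting list control group". The CPG, HADS, UAL and LiSat-9 are scheduled in both groups at all five visits.

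**The concern.** The analysis and the measurement schedule do not fit together. Pooling works by aligning each arm to the start of its own programme: t1, t2, t3 in the intervention group correspond to t3, t4, t5 in the waiting list group. The outcomes follow that alignment. The coping and cognition questionnaires do not, because in the waiting list group they are absent at the first two of the three aligned visits.

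At stake is part of the secondary aim: whether people with dysfunctional cognitions and coping beforehand benefit most, and whether change in coping and cognitions goes with benefit. If the schedule is followed as written, the waiting list arm cannot enter that analysis in the stated form. A score not taken at t3 or t4 cannot be recovered later.

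**Working it through.** **Step 1. Align the visits.** Under Participants and procedure, the control group is invited for the programme after the 6-month measurement, so t3 is its pre-programme visit. The Abstract gives the programme about 3 months, which makes t4 (9 months) its end-of-programme visit and t5 (12 months) its follow-up. Table 2 supports this: the satisfaction questionnaire is given to the intervention group at T2 and to the waiting list group at T4, each at the end of that arm's programme. That row also shows that the columns of Table 2 have been read correctly.

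**Step 2. Compare visits needed with visits scheduled (CSQ, PCI, PCL).**

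| Role in the pooled analysis | Intervention group | Collected? | Waiting list group | Collected? |
|---|---|---|---|---|
| Immediately before programme | t1 | yes | t3 | no |
| End of programme | t2 | yes | t4 | no |
| Follow-up | t3 | yes | t5 | yes |

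Four of the six required group-visits are covered. In the waiting list group:

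- level immediately before the programme: needs t3, missing;
- change during the programme: needs t3 and t4, both missing;
- change after the programme: needs t4 and t5, t4 missing.

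**Step 3. Count the people.** The Power analysis section gives 24 per arm (48 in total) and 20% dropout: 48 / (1 - 0.20) = 60. It does not state an allocation ratio; equal allocation is inferred from the 24 per arm, giving 60 / 2 = 30 per arm.

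| | Both arms, as the Discussion promises | With scores at all required visits under Table 2 |
|---|---|---|
| Randomised | 60 | 30 |
| After 20% dropout | 48 | 24 |

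The factor of two in the Discussion is therefore not reproduced for this analysis. With the questionnaires added at t3 and t4 for the waiting list group, coverage becomes six of six and the factor is restored.

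**Step 4. What the loss means, as an illustration.** The plan gives no target for this exploratory analysis. As a yardstick, the smallest correlation detectable with 80% power at two-sided 0.05 (Fisher z) is r = tanh[(1.960 + 0.842) / sqrt(n - 3)]:

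- n = 60: tanh(2.802 / 7.550) = 0.36
- n = 48: tanh(2.802 / 6.708) = 0.39
- n = 30: tanh(2.802 / 5.196) = 0.49
- n = 24: tanh(2.802 / 4.583) = 0.55

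**Step 5. What remains in the waiting list group.** Scores exist at t1, t2 and t5. The nearest pre-programme score is t2, at 3 months, against a programme that starts after 6 months: a gap of about three months. A t2-to-t5 change therefore spans roughly three months of waiting, three of programme and three of follow-up. It cannot be split into change during and change after.

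**The case against.** The best defence is that the waiting list group is not without data. It has two scores before its programme and one after, so a pre-to-post change can be formed. The Data analysis section also does not name the visit that supplies the baseline coping score, so t1 or t2 could serve for the question of who benefits most. This stands in part. It rules out saying that the waiting list group has no pre-to-post change at all. It does not rescue the stated analysis, whose window for that group begins at t3 and which separates change during the programme from change after it.

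It may also be said that a journal article condenses the full protocol. That would excuse an omission. Here two explicit statements in the same article conflict, and all three questionnaire rows agree with one another.

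A reader might infer more than the document supports:

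- *That the whole pooled analysis fails for half the sample.* It does not. Demographic and lesion characteristics are recorded at t1 and outcomes at every visit, so that part can be pooled across both arms.
- *That a known amount of attenuation follows from using t2.* The article quotes stability coefficients of 0.45 to 0.86 over eight weeks (CSQ) and 0.51 to 0.73 over two weeks (PCL). These include ordinary measurement error, which a t3 score would carry too, so they do not isolate the extra loss. They show only that an older score is an imperfect substitute.
- *That a randomised 6-month comparison of coping is lost.* None is planned. The between-group analysis covers the CPG, HADS, UAL and LiSat-9.
- *That the trial's main conclusion is at risk.* The affected analysis is labelled exploratory and post hoc, and the t1 to t3 comparison of the arms does not use these scores.

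**Conclusion.** The contradiction is real and confined to the coping and cognition part of an exploratory analysis. Under Table 2, the level immediately before the programme, the change during it and the change after it are unavailable for the whole waiting list arm: about 30 of 60 participants, or about 24 of 48 after dropout. The Discussion's claim of doubled numbers is not met for the analysis as stated; only a cruder t2-to-t5 analysis could use both arms.

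This rests on equal allocation and on the waiting list programme starting soon after t3 and lasting about three months, as the article describes. It should be fixed, because the plan cannot be carried out as written and the missing scores cannot be obtained afterwards. It does not threaten the primary comparison, the secondary outcome comparisons or the long-term analysis in the intervention arm.

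**What to change.** In Table 2, for the CSQ, PCI and PCL, change the T3 entry from X^I to X and add X^C at T4. Both visits already take place in the waiting list group. The change should be made before the first waiting list participant reaches t3.

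Cost: 44 + 33 + 39 = 116 items at each of two visits, or 2 × 116 = 232 more items per person, for at most 30 people. The waiting list group would complete the set five times instead of three. The extra burden looks modest, but that is a judgement, since the article gives no figures on respondent burden.

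If the sponsor declines:

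- limit the analysis of change during and after the programme to the intervention group;
- state that t2 serves as the waiting list group's baseline, that it lies about three months before the programme, and that a t2-to-t5 change includes waiting time;
- qualify the statement in the Discussion so that it no longer promises doubled numbers for the coping and cognition analysis as stated.

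This alternative costs only wording, but it gives up the fuller analysis in half the sample.
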